VitD deficiency in ethnic minorities in the UK is well known and is described as an unrecognized epidemic (Darling, 2020). In the UK, 50% of SAs and 33% of Black ACs demonstrate vitD deficiency, whereas 17.5% of White Caucasians do (Sutherland et al., 2021), which is primarily due to more subcutaneous pigmentation that absorbs ultraviolet B from sunlight and reduces vitD production in the skin and at high latitudes in the UK (Yousef et al., 2023). This situation is worse in East London. In Tower Hamlets, a borough of East London, 80–97% of the residents are thought to have vitD deficiency, significantly higher than the national population at 50% (Towerhamlets.gov.uk, 2017). An inverse association of serum 25(OH)D levels with insulin resistance was observed in healthy adults (Yin et al., 2022) and diabetic patients (Abubaker et al., 2022). Recent evidence from systematic reviews and meta-analyses of randomized controlled trials (RCTs) suggests that vitD supplementation may help reduce fasting plasma glucose concentrations, HbA1c levels, and insulin resistance in patients with T2DM (Afraie et al., 2024; Farahmand et al., 2023). However, little evidence is available that focuses on ethnic minority groups or residents in East London, indicating that AC and SA communities are underrepresented in the evidence base concerning diabetes and vitD.

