## Method

This is an acute, randomized, repeated measures crossover trial. Figure 1 shows the study flow chart. The proposal was approved by the Senate Research Ethics Committee at City St George's, University of London (Ref ETH2223-2000). This study was registered with ClinicalTrials.gov (identifier: NCT06241976). The recruitment period of the study is between 1 November 2023 and 31 March 2025 in London, UK. The informed consent is obtained from all participants before taking part in the study.

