**Figure 1. fig1-02601060251356528:**
[figure not shown]
Study flow diagram.

Study status: A) participant recruitment will be completed at the end of March 2025; B) data collection will be completed at the end of March 2025; C) results are expected in April and May 2025. None of these stages have already been completed when the manuscript was submitted.

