## Recruitment

There are a few methods of recruiting participants. We will recruit staff and students who live in East London with gatekeeper permissions from the Dean of the school. Recruitment adverts will be circulated to staff and students at City St George's, University of London. There are 19975 students, among whom 64% are from the UK, and a large proportion of students are from different London boroughs, including the East London area. Each year, many staff and student projects recruit participants successfully in this way. In addition, we recruit participants from local communities in East London with gatekeeper permission. We will contact local ethnic communities, including the Bangladeshi Community, London Central Mosque, Bangladesh Embassy and Indian & Bangladesh Hindu Community East London, etc. We will also recruit participants via social media, including Meta (formerly Facebook), X (formerly Twitter), Instagram, and LinkedIn. To encourage taking part in the study, participants will receive a shopping voucher worth £20 per visit as a gesture of thanks and an incentive.

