## Study design

The participants will consume a glucose drink (75 g glucose in 300 ml water, 281 kcal) used for the OGTT (Eyth et al., 2023) and pure OJ (Tesco 100% Pure Squeezed Orange Juice Smooth 300 ml containing 129 kcal, 30 g sugar, 0.3 g fiber, 1.8 g protein and 90 mg vitamin C) on separate occasions with at least 48-h interval and at random order. The two drinks were chosen rather than meals because of fewer facilities needed to cater to participants, fewer potential food hygiene issues, and being more acceptable to participants from different ethnic backgrounds. The participants fast for 8–12 h. The blood glucose concentration is measured via a HemoCue Glucose 201+ Analyzer (Health-care Equipment & Supplies, Surrey, UK) at 0, 30, 60, 90, and 120 min before and after drink consumption by finger prick. Seven milliliters of fasting blood will be collected via phlebotomy on the first visit. If blood collection is unsuccessful on the first visit, it will be attempted on the second visit. The plasma is separated by centrifuging the blood sample at 2000 × g for 10 min and stored at −20°C until analysis of the metabolic parameters (refer to the section on outcome measures).

Participants are asked to consume the drinks (either a glucose drink or OJ) within 5 min in the resting area outside the clinic room. The researcher will record the start and end times of consumption. During the 2-h study period, the participants are asked to remain sedentary and refrain from eating or drinking while sitting in the resting area. On the evening before each study visit, participants are encouraged to consume similar meals across both visits, ensure adequate sleep, and avoid alcohol consumption and strenuous physical activity. On the study visit, the researcher will collect information on the participant's dinner from the previous evening, hours of sleep, alcohol intake, and physical activity.

The name, email/mobile (for appointment purposes), sex, age, and ethnicity of the participants are also collected. The research assistant (ST) will generate the allocation sequence, enroll participants, collect consent forms, assign participants to interventions and conduct the trial. The study is not blind to the researcher and participants but is blind to the statistician (SI) who will analyze the data.

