## Data analysis

The sample size was calculated using G*Power software (version 3.1.9.7; Heinrich Heine University, Düsseldorf, Germany), based on F-tests for ANOVA: repeated measures, between-subjects factors. This study aims to achieve an effect size of 0.25 in the PGRs among three ethnic groups, considering that the response is taken from five different time points with 30-min intervals for each person, and to achieve 80% power in the study, we will need 32 people in each group (n = 96 in total) at the 5% level of significance. The details of the sample size calculation can be found in Appendix 3. Considering the acute nature of the study, we believe 10% of the attention is sufficient; therefore, the target number of recruitments is 106 participants. Data normality will be assessed using the Kolmogorov–Smirnov test. Continuous variables with a normal distribution will be presented as means ± standard deviations, while non-normally distributed data will be reported as medians and interquartile ranges. Categorical data are presented as numbers and percentages. The iAUC is calculated using approximated trapezoidal numerical integration (Chlup et al., 2008), and only the incremental area above the fasting level will be included. The association of plasma 25(OH)D concentrations and the iAUCs and PVs, respectively, will be analyzed using a multiple linear regression model adjusted by age, gender (using dummy variables), BMI, and body fat percentages, including all participants, as well as in different ethnic groups. The iAUCs and PVs concentrations between ethnic groups after each drink consumption will be analyzed by one-way ANCOVA adjusted by confounding factors including fasting glucose concentration, age, sex, BMI, and body fat percentage. The correlation of iAUCs and PVs between the two drink consumptions is analyzed by Pearson's correlation to identify the difference in the pattern of PGRs to different drink consumptions. Other continuous variables (e.g. plasma 25(OH)D etc.) between ethnic groups will be analyzed by one-way ANCOVA adjusting confounding factors (age, gender, BMI and body fat percentage). Categorical variables, e.g. gender, the percentage of patients with vitD deficiency etc., are compared between ethnic groups via Chi-square tests. The statistical significance will be reported with a *P*-value (significance was set at *P* ≤ 0.05, two-tailed) and a 95% confidence interval. The statistical software IBM SPSS 29 will be used to analyze the data. The percentage of missing data is expected to be low based on our previous experience. Therefore, regression imputation is used to address missing data. Both intention-to-treat analysis and per-protocol analysis will be used for the data analysis.

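### The ethnic comparisons of 25(OH)D and of deficiency omit season of blood draw, although each person is sampled once in a 17-month window and nothing balances draw dates across groups

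*Protocol article*

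**What the plan says.** All references are to the protocol article.

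- **Window.** Method: "The recruitment period of the study is between 1 November 2023 and 31 March 2025 in London, UK". The status note under Figure 1 adds that "data collection will be completed at the end of March 2025", so the blood draws fall in the same window.
- **One sample per person.** Study design: "Seven milliliters of fasting blood will be collected via phlebotomy on the first visit". A failed draw is tried again at the second visit.
- **Sunlight.** The Introduction explains the ethnic gap in deficiency chiefly by "more subcutaneous pigmentation that absorbs ultraviolet B from sunlight and reduces vitD production in the skin and at high latitudes in the UK".
- **Ethnic comparison of 25(OH)D.** Data analysis: continuous variables other than iAUC and peak value, with plasma 25(OH)D as the named example, "between ethnic groups will be analyzed by one-way ANCOVA adjusting confounding factors (age, gender, BMI and body fat percentage"). The list is closed and has no season or date.
- **Deficiency.** The same section compares the percentage deficient between groups by chi-square, without covariates.
- **Primary regression of iAUC and peak value on 25(OH)D.** The same four covariates, fitted in all participants and within ethnic groups. The Abstract repeats the list.
- **Balance.** Only drink order is randomized (Randomization). No section schedules or stratifies draws by calendar time, and the Limitations do not mention season.

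**The concern.** If vitamin D status depends on sunlight, a single reading reflects partly the person and partly the date. Ethnicity is observed, not allocated, so randomizing the drink order does nothing to equalize draw dates between White, South Asian and African-Caribbean participants. A group that happens to be drawn more often in summer will look better supplied. The four adjustment variables cannot correct this, and the chi-square test corrects for nothing.

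Differences between ethnic groups in variables relating to vitamin D status are stated secondary outcomes. The Implications section wants the results to inform education, fortification and a later trial. A difference that is partly a calendar effect would weaken that use. This is not a detail left to another document: the article writes out the covariates and labels them as the confounders.

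**Working it through.** **Window.** November 2023 to March 2025 is 2 + 12 + 3 = 17 calendar months: two winters and one summer. Taking April–September 2024 as summer, an even flow of participants gives a summer share of p = 6/17 = 0.353.

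**Group size.** The plan's figure is 32 per group, 96 in total. With f = 0.25, three groups, five measurements and an assumed correlation of 0.5 (the article text does not give one), the noncentrality is f²·N·m/[1 + (m − 1)ρ] = 0.0625 × 96 × 5 / 3 = 10. Power on (2, 93) degrees of freedom is then 0.802. The 96 is reproduced and is not affected by this point.

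**Gap in summer share from chance alone.** SE of the difference between two groups = √[2p(1 − p)/32] = √(2 × 0.353 × 0.647/32) = 0.12.
- The 95% range is ±1.96 × 0.12, about ±0.23.
- By simulation, a given pair differs by 20 points or more in about 9% of trials, and at least one of the three pairs does so in about 20%.
- A 40-point gap is 0.40/0.1195 = 3.3 SE, so it would need a systematic difference in timing.

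**Spurious difference in 25(OH)D** = seasonal shift × gap in summer share. The shift is an assumption (0.5–1.0 within-season SD); the article gives none.

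| Gap in summer share | Shift 0.5 SD | Shift 1.0 SD |
|---|---|---|
| 20 points (chance level) | 0.10 SD | 0.20 SD |
| 40 points (systematic only) | 0.20 SD | 0.40 SD |

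For scale, the SE of a difference between two groups of 32 is √(2/32) = 0.25 SD. The chance-level error is therefore 0.4–0.8 of a standard error.

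**Effect on the test.** 4,000 simulated trials per scenario, 32 per group, no true ethnic difference. Assumed within-season SD 20 nmol/L and summer–winter gap 10 or 20 nmol/L, which is again 0.5 or 1.0 SD.

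| Expected summer shares | Type I error, season omitted (gap 10; 20) | Season in the model (gap 10; 20) |
|---|---|---|
| 35/35/35% | 4.8%; 5.7% | 5.2%; 5.6% |
| 45/35/25% | 5.8%; 9.3% | 5.1%; 4.9% |
| 55/35/15% | 9.1%; 22.2% | 4.4%; 5.1% |

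With equal expected shares the test keeps its level: chance imbalance displaces the estimate in a given trial and adds noise, but does not inflate error over repeated trials. Inflation needs expected shares that differ by group.

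**Primary regression.** If season shifts PGR by c SD and 25(OH)D has no effect, the spurious slope per SD of 25(OH)D is c·A·p(1 − p)/√[A²p(1 − p) + 20²], with A the seasonal gap.
- c = 0: slope 0.
- c = 0.2: 0.02 (A = 10) to 0.04 (A = 20).
- c = 0.5: 0.06 (A = 10) to 0.10 (A = 20).

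**Price of adjusting that regression.** With an even split and a 1 SD shift, season adds 0.5 × 0.5 × 1² = 0.25 to a within-season variance of 1, so it explains 0.25/1.25 = 20% of 25(OH)D variance. The SE of the slope grows by 1/√0.8 = 1.12, about 12%, unless season also explains PGR. With a 0.5 SD shift the figures are 0.0625/1.0625 = 5.9% and about 3%.

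**The case against.** **Timing by group.** A reader might infer from the Recruitment section that groups were enrolled in waves, because it names separate channels (for example "We will contact local ethnic communities, including the Bangladeshi Community, London Central Mosque, Bangladesh Embassy"). The article does not support this. It lists channels without order or dates, and all of them may have run throughout. A systematic gap is possible but not shown, so the 40-point row is only a what-if.

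**Share of the ethnic difference.** A reader might convert the Introduction's UK deficiency rates (50%, 33%, 17.5%) by probit into differences of 0.44 SD (South Asian vs African-Caribbean) and 0.93 SD (South Asian vs White), and conclude that season could account for up to 90% of the effect. That pairs the most extreme assumed bias (0.40) with the smaller contrast; against 0.93 the same bias is 43%. The rates are also national, while the same section puts deficiency in Tower Hamlets, an East London borough, at 80–97%. The percentage should not be used.

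**Primary outcome.** A reader might infer that the 25(OH)D–PGR slope is biased. That requires season to affect PGR too, and no section says so. If season moves only 25(OH)D, it supplies real exposure variation and adjustment costs precision. This objection stands, and limits the point to the secondary comparisons.

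**Reading of the Introduction.** It stresses pigmentation and latitude and does not mention season. Where pigmentation limits production, the seasonal swing may differ by group, and an additive season term would correct only in part. That stands as a limit of the remedy, not as a reason to omit season.

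**Open list.** The covariate list of the iAUC and peak-value ANCOVA is worded so that more terms could be added. The 25(OH)D list is not, and the point concerns that list and the chi-square test.

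**Conclusion.** The point holds for the secondary ethnic comparisons of 25(OH)D and of deficiency. One reading per person on an uncontrolled date within 17 months, a determinant linked to sunlight, and written analyses without season leave these comparisons open to differences in draw timing.

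The likely size is modest: 0.1–0.2 SD, resting on an assumed seasonal shift of 0.5–1.0 SD and a 20-point gap in summer share, which arises by chance between at least one pair of groups in about a fifth of trials. Larger errors, and a clear rise in false positives, need a systematic difference in timing that the article neither states nor rules out. For the primary regression, confounding by season is conditional on an effect of season on PGR and is not established. The sample size is not affected. The change is worth making because it is cheap and removes an avoidable ambiguity.

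**What to change.** - Add season of blood draw to the 25(OH)D ANCOVA, as two levels or as sine and cosine of the draw date.
- Compare deficiency by logistic regression on ethnicity and season, not by chi-square alone.
- Tabulate draw dates by ethnic group, so that readers can see any imbalance.
- Keep the primary 25(OH)D–PGR regression as written and add a season-adjusted model as a sensitivity analysis.
- Record the change before the statistician analyses the data.

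**Cost.** 1–2 degrees of freedom per model, and no change to sample size or procedures. The draw date is needed; the article does not say that it is recorded, but visits are by appointment, so it should be available. In the season-adjusted regression the interval for the 25(OH)D slope widens by about 12% if season explains 20% of 25(OH)D variance. This will be felt most in the within-group fits, which have about 32 people and already carry five predictors.

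### Regression imputation with no stated variance correction can make the intervals for the primary 25(OH)D slope too narrow: slightly at low missingness, materially near 10%

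*Protocol article*

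**What the plan says.** The protocol article, Data analysis, gives a method and a reason for it. The reason is "The percentage of missing data is expected to be low based on our previous experience", and the conclusion drawn from it is that "regression imputation is used to address missing data". The article does not name the variables to be imputed, the predictors, any residual term or the number of imputations. It plans no missing-data sensitivity analysis, although it does plan both intention-to-treat and per-protocol analyses.

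The same section sets a two-sided 5% level with 95% confidence intervals. It specifies the primary analysis as a linear regression of iAUC and peak value on 25(OH)D, adjusted for age, gender, BMI and body fat, in all participants and in each ethnic group. On losses it says "we believe 10% of the attention is sufficient; therefore, the target number of recruitments is 106 participants", where attrition is evidently meant. Study design provides for a failed blood draw: "If blood collection is unsuccessful on the first visit, it will be attempted on the second visit".

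**The concern.** A value predicted from a regression carries no new information and, without a residual term, no scatter. If it is analysed as an observation, the sample looks larger and the residual variance smaller than they are. When the predicting model contains the other half of the association under study (25(OH)D for a missing glucose outcome, or the outcome for a missing 25(OH)D), the standard error of the slope is understated.

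That slope is the trial's primary quantity, so the promised 5% level and 95% intervals would not be met. The regressions within ethnic groups, with about a third of the participants each, have the least room for it.

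Gaps can arise in both variables. The drinks are taken on separate visits, so leaving after the first visit loses one whole glucose curve. Failed phlebotomy at both visits loses 25(OH)D.

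The stated reasoning is also weak. A low missing rate bounds the damage from a poor method, but it is equally a reason for simply analysing complete cases.

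**Working it through.** **Inputs from the article (Data analysis).** 96 evaluable, 32 per group; 106 recruited; nominal two-sided level 5%. The primary model has p = 6 parameters: intercept, 25(OH)D, age, gender, BMI and body fat.

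**Assumptions.** Missing rates of 2, 5, 10 and 20%, since the article gives no number; data missing completely at random; assumed covariate correlations; 106/3 ≈ 35 participants per ethnic group.

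**1. The plan's own figure.** The sample size reproduces if the correlation between time points is taken as 0.5, which the article does not state. The noncentrality is λ = f²·N·m/(1+(m−1)ρ) = 0.0625 × 96 × 5/(1 + 4 × 0.5) = 10. A noncentral F on 2 and 93 degrees of freedom then gives power 0.802. Adding 10% gives 96 × 1.10 = 105.6, so 106. This fixes the n used below. The article gives no figure for the effect of imputation.

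**2. Closed form, missing outcome imputed from the analysis model.** The slope equals the complete-case slope, and the residual sum of squares does not change. The residual variance is divided by n − p instead of n_obs − p, and the predictor information is counted for n people instead of n_obs. So

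width ratio = √[(n_obs − p)/(n − p)] × √(n_obs/n)

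type I error = P(|T| > ratio × t₀.₉₇₅,ₙ₋ₚ), with T on n_obs − p degrees of freedom.

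For 11 of 106 missing: √(89/100) × √(95/106) = 0.943 × 0.947 = 0.893. The effective critical value is 0.893 × 1.984 = 1.772, and the error is 8.0%.

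**3. Closed form beside simulation** (8000 runs, true slope zero, simulation standard error 0.24 points).

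| n | Missing | Width ratio | Error, closed form | Error, simulated |
|---|---|---|---|---|
| 106 | 2 (2%) | 0.981 | 5.5% | 5.5% |
| 106 | 5 (5%) | 0.951 | 6.2% | 6.5% |
| 106 | 11 (10%) | 0.893 | 8.0% | 8.0% |
| 106 | 21 (20%) | 0.796 | 11.8% | 12.7% |
| 35 | 1 (2%) | 0.968 | 5.8% | 6.2% |
| 35 | 2 (5%) | 0.937 | 6.6% | 6.6% |
| 35 | 4 (10%) | 0.874 | 8.6% | 9.5% |
| 35 | 7 (20%) | 0.779 | 12.5% | 13.5% |

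A second simulation of the same kind gave 5.2%, 6.0% and 8.0% at 2, 5 and 10% missing for n = 106, and 6.1%, 6.6% and 9.2% for n = 35.

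**4. Dependence on the imputation model** (n = 106, 10% missing unless stated).

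- Outcome imputed with the other drink's response as an extra predictor: 7.5%.
- 25(OH)D imputed from covariates and the outcome: 8.3%.
- Single imputation with a random residual added: 7.3% for the outcome, 7.4% for 25(OH)D. The residual reduces the problem but does not cure it.
- 25(OH)D imputed from covariates only: 5.2 to 5.3% across 2 to 20% missing. Little inflation.
- Outcome imputed without 25(OH)D: 4.5 to 5.0% across 2 to 20% missing, but a true slope of −0.30 is estimated on average as −0.27, and 6.6% of the 95% intervals miss the true value.

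**5. The alternatives** (3000 runs, simulation standard error 0.4 points, 2 to 20% missing).

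- Multiple imputation, 20 imputations with Rubin's rules: 4.0 to 5.4% at n = 106 and 4.2 to 5.4% at n = 35.
- Complete cases: about 4.9 to 5.3% at n = 106 and 4.4 to 6.2% at n = 35.

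Both agree with 5%, allowing for simulation error.

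**The case against.** The strongest reply has three parts.

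First, the article never says that imputation is single, nor that the imputation model equals the analysis model. It condenses a fuller document where both may be settled. This stands as a limit on the claim: a single fill-in is the ordinary sense of the term, not the plan's wording. It does not remove the point, because the article itself names the method and gives low missingness as its reason.

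Second, the excess is not unconditional. Step 4 shows one imputation model with almost no inflation and another that fails through attenuation. This stands too. Without a named model, though, nothing steers the analyst away from the harmful versions.

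Third, at the rates the article expects, the effect is small. Drink order is randomised, so even if the whole 10% allowance left after the first visit, each drink's outcome would be missing for about 5%, where the error is about 6 to 6.5%. The article also calls the study observational and meant to inform a later trial. This is fair and sets the weight of the point.

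A reader might go further and infer that the error rate more than doubles. It does reach 12.4% (n = 96) and 13.1% (n = 32) in simulation if 10% of outcomes and, independently, 10% of 25(OH)D values are imputed. That would leave 1 − 0.9 × 0.9 = 19% of participants with a gap. The documents do not support this scenario: missingness is expected to be low, the total allowance is 10%, a failed draw is tried again at the second visit, and 96 is already the number after losses.

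**Conclusion.** The point holds in a conditional form. Read in its usual sense, the stated method understates uncertainty in the primary 25(OH)D regression whenever the imputation model contains the other variable of the association. In all participants the type I error is then about 5 to 6.5% at 2 to 5% missing and about 8% at 10%. In one ethnic group it is about 6 to 7% and about 9%. These figures assume outcomes imputed from the analysis model, data missing completely at random, and missing rates and correlations that are not in the article.

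The documents do not support saying that the plan specifies single imputation in so many words, that the 5% level is exceeded whatever the imputation model, or that the error doubles. The change should be made because the method is named, bears on the primary result and is cheap to replace. At low missingness it is unlikely by itself to overturn the conclusions.

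**What to change.** Replace the sentence on regression imputation with multiple imputation, for example 20 imputations combined by Rubin's rules. Name the imputation model: the outcome, 25(OH)D, ethnicity, the other drink's response and the analysis covariates. For the regressions within ethnic groups, impute within the group, as the n = 35 check did, so that the imputation does not pull the group slopes together. Make complete cases the sensitivity analysis.

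Alternatively, state in advance that complete cases are the primary analysis if missingness is below about 5%.

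The cost is a sentence or two in the plan, minor extra analysis work and slightly wider intervals. Sample size and trial conduct do not change.
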